### Perspectives and perceptions about predictive testing in the treatment of depression

2.4

This part of the PROMPT project seeks to identify perspectives and perceptions that may play a role when patients and professionals engage in a shared decision making (SDM) process on the question whether to apply an algorithm to aid decision making on the use of antidepressants. SDM requires engagement of health care professionals and facilitates patient empowerment by taking a patient’s wishes, values, beliefs, attitudes and perspectives into account (14–16). We approach this question on the possible value of an algorithm in treatment settings by employing two methodological approaches, qualitative focus groups and quantitative (online) surveys. Taken together, these two approaches will allow us to learn about the perspectives of different stakeholders participating in MDD treatment toward the assumed use of a treatment decision-aiding algorithm. It is anticipated that these results have the potential to foster translation into clinical practice, especially shared decision making processes.

#### MDD patients focus group

2.4.1

Employing an experience-driven bottom-up approach, patient focus groups will be conducted at all patient-recruiting PROMPT sites (Munster − Germany, Cagliari − Italy, Poznan − Poland) to learn about the perspectives of MDD patients toward the algorithm in a rather hypothesis-freeway (33, 34). Using a pre-developed protocol, MDD patients meeting the criteria for participation in the PROMPT phase 2 will be invited to take part in a 90 min group discussion together with 3–4 fellow patients of different sex, age, and MDD history. Trained moderators will lead through the three-step procedure. After a short introduction to share previous experiences with depression treatment, participating patients learn about the algorithm and are encouraged to freely voice and discuss their thoughts, concerns, hopes and perspectives before the session concludes with an overall summery. Details about the algorithm are provided by means of a graphical representation and moderators are instructed to seek a broad exploration of the issues raised by the participants and to employ a series of follow up questions targeting specific areas of potential relevance. All focus groups will be audio recorded. Patient anonymity is maintained by choosing pseudonyms during the discussion and by removing private information from the subsequently generated transcripts. Following transcription of all audio recordings, anonymized transcripts will be further translated into English. Qualitative content analysis is conducted upon both, native language transcripts and English translations using MAXQDA^®^. Drawing on a transcript-based classification scheme, two different coders will analyze patients’ statements, focusing particularly on hopes or concerns associated with the algorithm, as well as on issues related to the decision-making process when deciding for or against the application of the decision-aiding algorithm that is being developed in the PROMPT project. To gain a broad understanding of the patient’s perspective on the algorithm and its application, we plan to conduct 4–5 focus groups at each site.

#### Online surveys

2.4.2

Employing a theory-driven top-down approach, we will further develop surveys to learn about the perspectives of MDD patients, psychiatrists, neurologists, general practitioners, scientists, and the general population in a more hypothesis-driven way. These surveys contain items presented to any participant group as well as target group specific items. For example, all participants are asked to complete a hypothetical decision-making scenario. In this scenario, the algorithm is introduced and participants have to choose. In case patients are addressed in the survey, they are asked whether they would agree to undergo testing. In case health care professionals are addressed, they would be asked whether they would recommend the use of a testing tool for their patients with depression. Completing the surveys, all participants are further asked to rate perceived importance of a set of SDM related variables for this particular decision scenario and to fill in scales meant to operationalize participants’ attitudes, beliefs or perspectives about genetics more generally. All surveys will be provided in English and in the different native languages of the PROMPT-Consortium participating countries and distributed either as a link to a REDCap based online version or as a paper version at all PROMPT Sites (French, German, Italian, Polish and Spanish). Using the R statistical environment (35), we will run linear mixed effect models on a pre-processed and random forest imputed dataset (36). Analyses will be conducted for each participant group, as a whole and in sex-specific manner.

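### The survey models run on one random-forest-imputed dataset with no stated allowance for imputation uncertainty, so standard errors will be too small by an amount that depends on the missing-data rate

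*Protocol article*

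**What the plan says.** Section 2.4.2 of the protocol article gives the survey analysis in one sentence: "we will run linear mixed effect models on a pre-processed and random forest imputed dataset". The noun is singular, and no pooling step or other allowance for imputation uncertainty is mentioned. The section then adds: "Analyses will be conducted for each participant group, as a whole and in sex-specific manner".

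It describes three kinds of response:

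- **A hypothetical choice.** "In this scenario, the algorithm is introduced and participants have to choose". For patients, "they are asked whether they would agree to undergo testing"; for health care professionals, "they would be asked whether they would recommend the use of a testing tool for their patients with depression".
- **Importance ratings.** Participants "rate perceived importance of a set of SDM related variables for this particular decision scenario".
- **Attitude scales** about genetics in general.

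On the instruments themselves it says: "These surveys contain items presented to any participant group as well as target group specific items". It does not name the dependent variable of any mixed model, and it does not give the response format of the choice item.

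**The concern.** When a missing answer is replaced once by a prediction and the dataset is then analysed as complete, the model counts that prediction as a real observation. Two things go wrong. The sample size is overstated. The residual variance is also understated, because a predicted value lies on the fitted surface and carries no scatter of its own. Both make the standard error too small.

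The article presents the surveys as the more hypothesis-driven of its two approaches to stakeholder perspectives, and section 2.4 expects the results to help translation into practice. Differences between sexes, or associations with the decision to use the algorithm, would then be declared too readily. The nominal 5% error rate would not be the actual one.

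**Working it through.** **Inputs.** From the article: a linear mixed model on one random-forest-imputed dataset. The article gives no survey sample size, missing-data rate, effect size or power, so there is no planned figure to reproduce. Everything below is an illustration under assumptions: an outcome rating missing completely at random at 5%, 10%, 20% or 30%; two groups differing by 0.4 SD; one auxiliary variable explaining a quarter of the within-group variance; and a fill-in by the fitted conditional mean, standing in for a deterministic random-forest prediction. The analysis model is an ordinary two-group regression, not a mixed model.

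**Closed form.** Set the within-group variance to 1, of which 0.25 is explained by the auxiliary variable and 0.75 is residual. Let m be the missing fraction.

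- Variance that the naive analysis uses (times a common factor): imputed values carry only the explained part, so (1 − m) × 1 + m × 0.25 = 1 − 0.75m.
- Actual sampling variance (same factor): the explained part is averaged over everyone, the residual part only over those observed, so 0.25 + 0.75/(1 − m).
- Ratio of reported to true standard error: r = √[(1 − 0.75m) / (0.25 + 0.75/(1 − m))].
- Approximate coverage of a nominal 95% interval: 2Φ(1.96r) − 1.

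| m | 1 − 0.75m | 0.25 + 0.75/(1 − m) | r | coverage |
|---|---|---|---|---|
| 0.05 | 0.9625 | 1.0395 | 0.962 | 0.941 |
| 0.10 | 0.9250 | 1.0833 | 0.924 | 0.930 |
| 0.20 | 0.8500 | 1.1875 | 0.846 | 0.903 |
| 0.30 | 0.7750 | 1.3214 | 0.766 | 0.867 |

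**Simulation, n = 300, 2,000 replicates, same set-up.**

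| m | single-imputation coverage | 20 imputations with Rubin's rules | SE, single / multiple |
|---|---|---|---|
| 0.05 | 0.941 | 0.949 | 0.96 |
| 0.10 | 0.929 | 0.950 | 0.92 |
| 0.20 | 0.903 | 0.953 | 0.84 |
| 0.30 | 0.856 | 0.951 | 0.76 |

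The simulated ratios agree with r to within 0.01, and the coverages to within about 0.01. Intervals are too narrow by about 4% at 5% missing and 24% at 30% missing.

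**Other simulations.** One at n = 200 with a different regression (slopes 0.3 and 0.4; 3,000 replicates) gave single-imputation coverage of 0.927, 0.887 and 0.851 at 10%, 20% and 30% missing. Another at n = 200 gave 0.94, 0.92, 0.90 and 0.84 at 5% to 30%, with about 0.95 after pooling 20 imputations.

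**Does a linear model on a binary item also narrow intervals?** This was checked separately on complete data, with 20,000 replicates. With equal groups, n = 100 or 300 and yes-rates between 0.5 and 0.95, coverage was 0.942 to 0.951. With 240 against 60 participants it was 0.990 when the larger group had rate 0.5 and the smaller 0.9, and 0.855 with the rates exchanged. There is no systematic direction, so the narrowing result comes from the single imputation alone.

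**The case against.** The strongest reply is that this is a journal article that covers the survey analysis in a sentence. The number of imputations and the pooling rule are the sort of detail a fuller plan would hold, and a singular noun does not exclude multiple imputation. That stands as a caution about certainty. It does not remove the point, because the article chose to state its method, and the method as stated is one imputed dataset.

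It is also fair to say that the size is assumed. The simulations contain neither a random forest nor a mixed model, and at 5% missing the loss is negligible. All of that stands, which is why the size is given as a range.

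Two stronger readings are tempting, and the text does not support them.

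- **A reader might infer that a yes/no choice is being modelled as continuous.** The article names no dependent variable and no response format for the choice. Several importance ratings per participant are an equally natural outcome for a mixed model, with the choice as a predictor. Even if the choice were the outcome, the check above shows no general narrowing of intervals.
- **A reader might infer that all participant groups are stacked before imputation, so that answers are filled in to questions never put to some people.** Nothing says the groups are combined. The text refers to surveys in the plural and to analyses for each participant group.

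**Conclusion.** The point holds for the imputation. As written, the survey analysis treats imputed answers as observed, and its standard errors will be too small. Coverage of a nominal 95% interval would be about 0.94 at 5% missing, 0.92–0.93 at 10%, 0.89–0.90 at 20% and 0.84–0.86 at 30%. The corresponding false-positive rates (one minus coverage) are about 6%, 7–8%, 10–11% and 14–16% instead of 5%.

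These figures assume values missing completely at random in an outcome item, a deterministic fill-in and a simple regression. The true missing-data rate is not in the article, so the effect may be anywhere from negligible to material.

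The model for the choice item is a conditional matter only: a linear model is unsuitable if that item is a binary outcome, since fitted probabilities can then leave the 0–1 range. The surveys are ancillary. The MADRS primary outcome, the AUROC-based sample size and the external validation of the algorithm are untouched.

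**What to change.** In section 2.4.2, replace the single imputed dataset with multiple imputation using a random-forest engine, for example 20 imputations. Fit the mixed model to each and pool by Rubin's rules. Run the imputation within each participant group and only on the items presented to that group; this rules out filling in questions that were never asked.

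Name the dependent variable of each mixed model. If the agree/recommend choice is a yes/no outcome of one of them, fit it with a mixed-effects logistic model.

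The cost is a little more analysis code, a few words in the plan and slightly wider intervals. No data collection changes. If a fuller plan already specifies multiple imputation with pooling, correcting the article's wording is enough.

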## Summary and conclusions

3

Our project aims at the development of a clinically useful algorithm model that integrates clinical data (wide range of symptomatology assessment, treatment side effects, presence of childhood trauma) and -omics data (genomic, pharmacogenetic, transcriptomic and miRNomic profiling) for the prediction of treatment response in MDD patients. The study results are framed in the context of precision psychiatry and personalized psychiatry to enable the tailoring of the right therapeutic strategy for the right person at the right time. To account for sex-specific MDD outcomes, all analyses in the project will be stratified according to sex to better understand the sex dimension of treatment response both in relation to biological factors, sex-related lifestyle and environmental factors. Moreover, our project deepens the knowledge and experience of the shared decision making process when using predictive algorithms to aid decision making in Psychiatry. Both, predictive computational tools and shared decision making processes constitute key components of the Personalized Psychiatry concept. The definition of TRD that we used is the commonly accepted clinical definition of two or more failed pharmacological treatments. Unfortunately, the absence of a validated definition of TRD is a major limitation from the viewpoints of translational research, treatment development, as well as clinical and policy decision-making. Indeed, for example neurostimulation techniques and evidence-based psychotherapy are not considered in the definition of TRD, which is a limitation of this definition. TRD patients should include particularly the non-remitters and recurrent MDD patients having a high probability to have a poor prognosis of the disorder. The pathway toward more targeted treatments in psychiatry requires a more precise delineation of the phenotype being evaluated, and this represents an important goal for current and future research in psychiatry.

## Data availability statement

The original contributions presented in the study are included in the article/supplementary material, further inquiries can be directed to the corresponding author/s.

## Ethics statement

The studies involving humans were approved by Ethik-Kommission Westfalen-Lippe der Ärztekammer Westfalen-Lippe, Münster, Germany (registration number: 2021-103-f-S). Based on the German ethics approval, local ethics approval was obtained at the other clinical trial sites. The studies were conducted in accordance with the local legislation and institutional requirements. The participants provided their written informed consent to participate in this study.
